## Abstract

Pectus excavatum (PE) is the most common deformity of the chest wall seen in children and adolescents. Besides its visible depression of the chest, this condition often causes functional impairments affecting the cardiovascular and respiratory systems, as well as postural issues. Additionally, the aesthetic aspect of the deformity can greatly impact the psychosocial well-being of those affected. This study aims to evaluate the effect of a tailored physiotherapy program on children and adolescents with PE, focusing on musculoskeletal, cardiopulmonary, postural, and balance measures. A total of 35 participants diagnosed with PE will be assessed using four complementary methods: myotonometry with MyotonPRO for the trapezius muscle involving all three fascicles and the pectoralis major muscle on both sides, cardiopulmonary exercise testing on a treadmill (including cardiopulmonary function), postural assessment with GaitOn, and static balance-stabilometry with PoData 2.0. These assessments will be performed before and three months after completing an individualized physiotherapy program, which participants will perform daily after proper instruction from a physical therapist. After three months, the initial and final results will be compared to determine how physical therapy influences treatment outcomes in patients with PE.

## 1. Introduction

Pectus excavatum (PE) is the most common deformity of the anterior chest wall in children, with an average incidence of 1 in 1000 newborns [1]. PE occurs five times more frequently in males [1]. It involves a concavity of the sternum and the costal cartilages caused by unbalanced growth of the costochondral regions of the anterior chest wall [2]. The inward bending of the chest wall has two main effects. First, it reduces chest volume, leading to decreased vital capacity (VC), forced vital capacity (FVC), forced expiratory flow (FEF25-75%), and forced expiratory volume per second (FEV1). Second, it compresses the heart, primarily at the right ventricle and atria levels. Heart compression results in incomplete filling of its chambers, which lowers the blood volume ejected with each heartbeat [3]. However, most patients maintain sufficient cardiac output at rest or during minimal effort and only experience insufficiency during intense activity. This limitation is likely more related to effort capacity restrictions than to restrictive lung dysfunction. Depending on the severity of the deformity, PE symptoms can range from minor to significant cardiopulmonary impairment [4]. In addition to ventricular systolic dysfunction, various types of arrhythmias may also be present [4].

PE is often linked with multiple axial and thoracic deviations, such as an asymmetrically developed anterior thorax, drooping shoulders, thoracic kyphosis, and sometimes even thoracic scoliosis, which is a secondary form of scoliosis [5]. These features are significant because the deviations mentioned influence the entire biomechanics of the rib cage and, indirectly, the entire body by altering the geometry and kinematics of the rib cage [6]. In turn, the rib cage plays a vital role in spine biomechanics, serving as a sturdy framework for muscle attachment and development that supports the stability and mobility of the entire body [6].

PE patients can be treated through various methods, including surgery or complementary non-surgical approaches, depending on their age and the severity of their condition [7]. For much of the twentieth and twenty-first centuries, surgery was the main treatment option. However, recent decades have seen the development of new non-surgical techniques to address this condition [8]. PE is believed to have a multifactorial origin, potentially involving genetic predisposition, connections to connective tissue disorders (such as Marfan syndrome), and debated environmental factors [7].

Complementary methods of conservative treatment include negative pressure therapy, which involves applying a suction cup to the front part of the chest, generating negative pressure on the concave area. The procedure is performed daily for about 60–90 min over at least 18 months. Vacuum bell therapy offers a non-invasive option, especially effective in younger patients, although results vary and depend on compliance; long-term data are still limited [9,10].

Physical exercise is another method to address PE. For these patients, the exercise program should also incorporate specific exercises for respiratory rehabilitation to enhance exercise tolerance. Pulmonary re-education helps increase awareness of how to properly manage breathing when lung function begins to decline, and how to decompress the sternum from vital organs such as the heart and lungs [11].

It should be noted that PE is associated with a series of axial deviations, most commonly kyphosis and thoracic scoliosis, and physical exercise helps to correct and balance the muscles involved. Therefore, the patient will improve overall posture by working on the stability and mobility of the thoracic cage, rebalancing its geometry, with the muscles involved physiologically supporting the spine [12].

There are no studies on changes in the length and elasticity of the rib cage muscles, which might be involved in the development of pectus excavatum in children and adolescents. This lack of research is one reason why we chose to focus on this topic in our paper.

Most likely, a complex mechanism causes pectus excavatum, involving not only genetic factors but also changes in growth cartilages and faulty biomechanics of the rib cage, which is a hypothesis we propose to investigate [13].

The study aims to evaluate children and adolescents with PE using four methods: myotonometry (with MyotonPRO) for the Trapezius muscle, assessing all three fascicles; the Pectoralis Major muscle on both the left and right sides; cardiopulmonary exercise testing on a walking/running treadmill (with cardio-pulmonary exercise function); postural assessment (with GaitOn); and static balance-stabilometry (with PoData 2.0), conducted before and 3 months after an individualized physiotherapy program.

## 2. Materials and Methods

This protocol study aims to evaluate a group of patients with PE treated with physical therapy to highlight the importance of physical exercise in managing this condition. Respiratory rehabilitation helps restore muscle elasticity and corrects the overall body posture. This study is conducted at the Emergency Clinical Hospital for Children in Timișoara, within the Medical Rehabilitation Department, from March 2025 to July 2026.

This article outlines the study protocol for assessing the efficacy and safety of a structured physiotherapy program in children with pectus excavatum; we also note that this is a prospective study. The main objective is to evaluate the effect of the physiotherapy program on respiratory function and body posture after three months of treatment, while secondary objectives include safety monitoring, assessment of postural improvements, and analysis of quality-of-life outcomes. By publishing this protocol, we aim to promote transparency in research methodology and provide a clear framework for the upcoming clinical study, the results of which will be shared in a later article.

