### 2.1. Sample Size Calculation

The effect size was 0.5, the type I error was α = 0.05, and power was 0.8. A total sample size of at least 35 patients was required. The sample size was calculated using G*Power 3.1.9.7 (Universitat Kiel, Kiel, Germany) with the Wilcoxon signed-rank test (matched pairs)

The within-group analyses will evaluate the effects over time. The evaluation of effect size was based on Cohen’s conventions for large effects [14]. The total sample size of our study (at least 35 patients) is in accordance with that calculated by Zielinski for patients who followed kinesiotherapy with the same statistical power and effect size (36 patients) [15].

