### 2.5. Statistical Analysis

Statistics will be performed using GraphPad Prism 5.0 for Windows. The descriptive statistics will be computed for all variables (mean and standard deviation). Before statistical applications, the normal distribution of values will be verified by the D’Agostino-Pearson normality test. The intragroup data (analyzed parameters at baseline and after the physical exercise program) will be compared with the paired *t*-test.

For the myotonometry, frequency, stiffness, decrement, stress relaxation time and creep of the trapezius and major pectoralis will be compared before and after the 3-month physical exercise program. VE and VO_2max_ will be analyzed at baseline and after the physical exercise program. Paired *t*-tests will be used to compare the intragroup data of the postural stability parameters (stabilometry data in the different testing situations). GaitOn postural analysis parameters will be measured before and after the 3-month physical exercise program.

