## 4. Discussion

The study will be randomized and will examine the characteristics of the trapezius and pectoralis major muscles, respiratory function, stability, and overall posture in children and adolescents with PE before and after a tailored physical therapy program lasting three months. The assessment of study participants will include four different testing methods: myotonometry, cardiopulmonary exercise testing (CPET), posture evaluation, and static balance analysis.

An excessively high position in the upper chest area may cause PE, and the pectoralis major muscle has a biomechanical role in lifting the sternum [25]. Consequently, the main hypothesis of this investigation will focus on assessing the tone of the pectoralis major and trapezius muscles, as well as examining any recorded discrepancies that might contribute to this condition. The study will explore changes in length, elasticity, muscle tone, and relaxation in muscles potentially involved in the development of the pathology through a non-invasive measurement method: myotonometry. No studies have been found in the literature that evaluate the properties of muscles involved in the development of PE. However, some evidence links thoracic kyphosis with this condition [6], prompting an analysis of the literature’s reported changes and a comparison with the findings of this study. Thoracic kyphosis appears as limited mobility of the thoracic spine caused by alterations in both non-contractile and contractile tissues [26].

Therefore, in a study conducted by Yeo et al., muscle tone was evaluated in the upper trapezius and pectoralis major muscles of patients with thoracic kyphosis using MyotonPro^®^ (Myoton AS, Tallinn, Estonia). Variations in the examined parameters were observed [27]. The measurement technique used in this study is similar to that in our research, with the MyotonPRO^®^ tip positioned vertically at the midpoint of the subjects’ upper trapezius and pectoralis major muscles.

The CPET evaluation of the study participants will assess the effect of sternal deformity on cardiopulmonary function and compare the results with those reported in existing literature.

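### The main question is stated in incompatible ways and no primary variable is named, so the alpha, power and N of 35 attach to no identifiable conclusion

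*Protocol article*

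**What the plan says.** The protocol article ranks its questions in three places, and they differ.

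- **Section 2 (Materials and Methods), main objective:** "The main objective is to evaluate the effect of the physiotherapy program on respiratory function and body posture after three months of treatment". The sentence continues: "secondary objectives include safety monitoring, assessment of postural improvements, and analysis of quality-of-life outcomes". Posture therefore sits at both levels.
- **Section 4 (Discussion):** "the main hypothesis of this investigation will focus on assessing the tone of the pectoralis major and trapezius muscles". Muscle tone does not appear in the main objective of Section 2.
- **Abstract:** the aim is described as "focusing on musculoskeletal, cardiopulmonary, postural, and balance measures", four domains with no order among them.

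Section 2.1 gives the design parameters, "The effect size was 0.5, the type I error was α = 0.05, and power was 0.8", and concludes: "A total sample size of at least 35 patients was required". It names a Wilcoxon signed-rank test for matched pairs but no outcome.

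Section 2.5 plans paired t-tests on the analysed parameters. For myotonometry, "frequency, stiffness, decrement, stress relaxation time and creep of the trapezius and major pectoralis will be compared before and after" the programme. VE and VO2max, stabilometry in the different testing situations, and the GaitOn parameters follow, all without ranking.

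**The concern.** A reader cannot tell what result would count as success: a change in a gas-exchange measure, in a posture measure, or in muscle tone. An analysis plan cannot settle this by following the protocol, because Section 2 and Section 4 point to different domains.

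Two things are at stake. First, the stated error rate and power describe one comparison; with no comparison identified, they protect no particular claim. Second, in a single-group before-and-after study with many measured parameters, an open choice of lead result allows it to be made after the data are seen. A significant finding chosen that way cannot be read at its nominal 5% level.

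**Working it through.** **1. Reproduce the sample size.** Inputs from Section 2.1: standardised paired difference dz = 0.5, alpha = 0.05, power 0.80, Wilcoxon signed-rank test. Sidedness is not stated. Power comes from the noncentral t distribution with n·ARE − 1 degrees of freedom and noncentrality dz·√(n·ARE), where the asymptotic relative efficiency (ARE) is 3/π for the Wilcoxon test with a normal parent and 1 for the paired t-test.

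| Test | Smallest N for 80% | Power at N = 35 |
|---|---|---|
| Wilcoxon, two-sided | 35 | 80.1% |
| Paired t, two-sided | 34 | 82.0% |
| Wilcoxon, one-sided | 28 | 88.2% |
| Paired t, one-sided | 27 | 89.5% |

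The figure of 35 is the first row: one two-sided test of one outcome. The arithmetic is sound; the outcome is missing.

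**2. Compare the statements of the main question.**

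| Domain | Section 2 | Section 4 | Abstract |
|---|---|---|---|
| Respiratory / cardiopulmonary | main | not in the main hypothesis | unranked |
| Posture | main and secondary | not in the main hypothesis | unranked |
| Muscle tone | not listed | main hypothesis | unranked |
| Balance | not listed | not in the main hypothesis | unranked |

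No row has a consistent rank, and no variable within any row is named as primary.

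**3. Count the candidate comparisons (assumption, shown as a range).** The documents state no count. Section 2.5 gives five myotonometry parameters and two CPET variables. Section 2.4.1 describes measurement at four sites on two sides. Section 2.4.3 lists five stabilometry items, or seven if right and left are separated. One measure per stabilometry situation is assumed, and GaitOn is left out because its number of parameters is not given.

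- Low: 5 parameters × 2 muscles + 2 + 5 = 17
- Middle: 5 × 4 sites, sides averaged, + 2 + 7 = 29
- High: 5 × 4 × 2 + 2 + 7 = 49

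**4. False positives if each were tested at 0.05 with no true change.** Expected number = 0.05m. Chance of at least one under independence = 1 − 0.95^m. The correlated case is simulated with equicorrelated paired t-tests at n = 35.

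| m | Expected | At least one, independent | At least one, correlation 0.7 |
|---|---|---|---|
| 17 | 0.85 | 58% | about 28% |
| 29 | 1.45 | 77% | about 34% |
| 49 | 2.45 | 92% | about 42% |

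**5. Power once the primary is fixed (dz = 0.5, N = 35, paired t).**

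- One primary at 0.05: 0.82 (Wilcoxon 0.80).
- Two primaries, either sufficing, Bonferroni at 0.025 each: 0.73 per endpoint. About 41 patients would be needed for 0.80.
- Two primaries, either sufficing, Holm, independent endpoints: 0.728 + (0.820 − 0.728) × 0.728 ≈ 0.79 per endpoint.
- Two primaries, both required: no alpha split. Joint power is 0.82 × 0.82 ≈ 0.67 if independent, and higher if they are positively correlated.

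**The case against.** The strongest reply is that this is a condensed journal article, and that error control across secondary measures is commonly left to an analysis plan. That stands: the absence of a multiplicity rule is not the finding. It does not answer the conflict over the main question, because the article does state its objective and does so inconsistently.

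A reader might also infer that the plan runs at least 49 unadjusted tests at 0.05. The text does not support that. Section 2.5 names the trapezius and pectoralis major without saying that fascicles and sides are analysed separately; Section 2.4.1 describes how readings are taken, not how they are tested. Section 2.5 gives no significance level: 0.05 appears only in the sample size section. Silence on adjustment is not a statement that none will be made. For these reasons the count is a range and serves only as illustration.

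Sections 2.4 and 4 also mention correlating the parameters. It would be tempting to count every possible pair as a test, but neither section says that all pairs will be examined or that p-values will be used.

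**Conclusion.** The point holds as a contradiction within the protocol. Posture is both main and secondary in Section 2, muscle tone is the main hypothesis in Section 4, and the variable for which 35 patients were sized is never named. That conclusion rests on the text alone.

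The size of the consequence rests on assumptions: separate or pooled sites and sides, one measure per stabilometry situation, and a 0.05 level for each test. Across the counts considered, the chance of at least one spurious result under independence runs from 58% to 92%. Correlation lowers it, but at 0.7 it is still more than five times the nominal 5%. GaitOn or further stabilometry parameters would raise the count.

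The sample size calculation itself is not in error. It supports one test of one named variable at dz = 0.5, provided that all 35 patients are analysed.

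**What to change.** 1. Make Section 2 and Section 4 state the same main objective, and place posture at one level only in Section 2.
2. Name one primary variable at 3 months. The choice is the sponsor's; VO2max (Section 2.5) or the lateral-view shoulder angle (Section 3) are examples that the article already mentions.
3. In Section 2.1, tie the effect size of 0.5 to that variable.
4. Label all other comparisons, and the correlations, as secondary or exploratory.
5. If two primaries are kept, say whether either or both must succeed. If either suffices, name the procedure and restate power per endpoint: about 0.73 with Bonferroni, or about 0.79 with Holm under independence. If both are required, keep 0.05 for each and restate the joint power.

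Section 2 dates the study from March 2025 to July 2026, so this should be a dated amendment made before any results are examined.

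**Cost:** a change of text and no extra patients for a single primary. Two primaries with a Bonferroni split mean accepting lower power or enrolling about 41. The downside is small: fewer results can be presented as confirmatory.

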### 2.1. Sample Size Calculation

The effect size was 0.5, the type I error was α = 0.05, and power was 0.8. A total sample size of at least 35 patients was required. The sample size was calculated using G*Power 3.1.9.7 (Universitat Kiel, Kiel, Germany) with the Wilcoxon signed-rank test (matched pairs)

The within-group analyses will evaluate the effects over time. The evaluation of effect size was based on Cohen’s conventions for large effects [14]. The total sample size of our study (at least 35 patients) is in accordance with that calculated by Zielinski for patients who followed kinesiotherapy with the same statistical power and effect size (36 patients) [15].

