### 2.2. Recruitment and Informed Consent

The study involves 35 patients with PE who wish to participate in a three-month physiotherapy program. Before the study begins, parents or guardians will be informed both verbally and in writing about all the details and milestones of the study.

The study is conducted in accordance with the Declaration of Helsinki and has been approved by the Ethics Committee of the “Victor Babeș” University of Medicine and Pharmacy in Timișoara, NO. 12/10.02.2025.

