#### 2.2.3. Discontinuing Criteria

Any subject who does not follow, interrupt, or deviate from the daily exercise program will be excluded from the study. Patients are also excluded if, during the study period, they suffer any injury that may affect their ability to adhere to the physiotherapy program.

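### The 35 is the minimum number of complete pairs but is also the planned number of participants, so the stated power of 0.8 is not protected against the plan's own exclusions

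*Protocol article*

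**What the plan says.** Section 2.1 gives the inputs: "The effect size was 0.5, the type I error was α = 0.05, and power was 0.8". The calculation was done in G*Power "with the Wilcoxon signed-rank test (matched pairs"), and the result is that "A total sample size of at least 35 patients was required". The same section later describes the study's own size as at least 35.

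Elsewhere the number appears without the qualifier. The Abstract says "A total of 35 participants diagnosed with PE will be assessed using four complementary methods", and Section 2.2 says "The study involves 35 patients with PE who wish to participate in a three-month physiotherapy program".

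Section 2.2.3 excludes from the study any participant who fails to follow, interrupts or deviates from the daily exercise programme. It adds: "Patients are also excluded if, during the study period, they suffer any injury that may affect their ability to adhere". By Section 2.3 the programme has two supervised weeks and is then continued daily at home for three months.

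Section 2.5 compares baseline with post-programme values by paired t-test. The article states no expected loss rate, replacement rule or over-recruitment.

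**The concern.** A matched-pairs calculation returns the number of children who contribute both a baseline and a 3-month value. If that number is also the number who start, the stated power holds only when essentially nobody is lost. Here the losses are not merely a hazard of follow-up. The plan prescribes them: as worded, the adherence rule has no tolerance threshold, and it applies to a daily programme lasting about three months.

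The study has one group and one comparison over time, so each excluded child removes one pair. What is at stake is the accuracy of the stated power. If children are excluded, a non-significant result would be reported beside a power of 0.8 that the analysed sample did not have.

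**Working it through.** **Inputs.** From Section 2.1: standardised paired effect d = 0.5, alpha = 0.05, target power 0.8, matched-pairs signed-rank test, N = 35. From Section 2.5: paired t-test for the analysis. Two assumptions are added. The test is taken as two-sided, which the article does not state, and the paired differences as normal.

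**Formulas.** For the signed-rank test, the effective size is n' = N × 3/π, where 3/π is its asymptotic efficiency relative to the t-test for normal data. Power comes from the noncentral t distribution with n' − 1 degrees of freedom and noncentrality d√n'. For the paired t-test, n' = N.

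**Reproducing the plan's figure.** At N = 35, n' = 35 × 3/π = 33.42, noncentrality = 0.5 × √33.42 = 2.89, and power = 0.8007. At N = 34, n' = 32.47, noncentrality = 2.85, and power = 0.7885. The smallest N reaching 0.8 is therefore 35, as stated. The one-sided version gives 28, so the two-sided reading is the one that fits. A simulation of the signed-rank test at 35 pairs also gave 0.801.

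**Power and detectable effect as pairs are lost from 35** (effect 0.5 for power; detectable effect at 80% power):

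| Pairs | Lost | Power, signed-rank | Power, paired t | Detectable d, signed-rank | Detectable d, paired t |
|---|---|---|---|---|---|
| 35 | 0 | 0.801 | 0.820 | 0.50 | 0.49 |
| 34 | 1 | 0.789 | 0.808 | 0.51 | 0.50 |
| 33 | 2 | 0.776 | 0.795 | 0.52 | 0.50 |
| 31 | 4 (about 10%) | 0.748 | 0.769 | 0.53 | 0.52 |
| 28 | 7 (20%) | 0.701 | 0.723 | 0.56 | 0.55 |

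Simulated signed-rank power agrees: 0.753 at 31 pairs and 0.699 at 28.

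The planned paired t-test needs 34 pairs, so the design has a reserve of one child under that test and none under the signed-rank test.

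**Enrolment that would keep 35 evaluable pairs.** N = 35/(1 − loss), rounded up. At 10% loss, 35/0.90 = 38.9, so 39. At 20% loss, 35/0.80 = 43.75, so 44.

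**The case against.** Several points on the other side are sound.

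- The arithmetic is right. A reader might infer that 35 was miscalculated; it was not, and it reproduces exactly.
- A reader might infer that enrolment is capped at exactly 35. The text does not go that far. Section 2.1 twice says at least 35, and the Abstract's 35 could be read as children assessed at both times. Section 2.2, however, most naturally reads as the number taking part, so the three places are at best ambiguous.
- A reader might say that a single exclusion breaks the design. That is true for the test used for sizing. Under the planned paired t-test, one exclusion still leaves 0.808, and it takes two to fall below 0.8.
- A reader might infer that several exclusions are likely, or that the stated power will certainly be missed. The article gives no loss rate, so neither can be shown. The inclusion criteria ask for availability at both evaluations, and the exclusion criteria screen out children unwilling to follow the plan. Both may reduce loss, although they apply at entry and cannot prevent the later deviation or injury that Section 2.2.3 anticipates.
- An article condenses a fuller protocol, and a replacement or over-recruitment rule may sit there. Its absence here is therefore not the complaint. The complaint is that printed statements about the number needed, the number taking part and mandatory removal do not fit together.

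The loss of power is also moderate: at 20% loss the detectable effect under the paired t-test moves from 0.49 to 0.55.

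**Conclusion.** The point holds in limited form. The 35 is a correct minimum number of complete pairs, but it also serves as the number of participants, while Section 2.2.3 removes some of them by rule. The stated power of 0.8 is therefore not protected against the plan's own exclusions. It is lost after one exclusion under the signed-rank test and after two under the paired t-test.

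The size of the shortfall depends on a loss rate that the article does not give. Over an assumed loss of about 10% to 20%, power is 0.75 to 0.70 (signed-rank) or 0.77 to 0.72 (paired t), and the effect detectable with 80% power is 0.53 to 0.56 or 0.52 to 0.55. These figures assume a two-sided test, normal paired differences and a true effect of 0.5. The point is a should-fix: the stated power needs qualifying, but the design does not fail because of it.

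**What to change.** 1. In Section 2.1, state that 35 is the number of evaluable baseline/3-month pairs, and make the Abstract and Section 2.2 agree with it.
2. In the same section, state a loss assumption and give the power or the detectable effect for the number of pairs expected under it. For example, with 31 to 28 pairs the planned paired t-test has power 0.77 to 0.72, or a detectable effect of 0.52 to 0.55.
3. Reconcile Section 2.2.3 with the analysis: separate stopping or deviating from the programme from removal from the analysis, so that a child with an available 3-month assessment is analysed. This concerns the analysis set only and leaves the clinical handling of such children as it is.

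The cost is a few sentences across these sections and no additional patients. The stated power becomes less favourable, and the estimate will include children who did not fully adhere, so it describes the programme as actually followed. If the investigators prefer to keep power at 0.8 on the signed-rank basis, the alternative is to enrol 39 at an assumed 10% loss or 44 at 20%.
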